Outcome measures	Primary outcome: Assessment of resting-state functional connectivity at baseline (T0) and at the end of NBCT (T1 after 4 weeks). Secondary outcome: Global cognitive and neuropsychological changes at T1, T2, and T3 vs. T0 when applicable according to Table 1. Secondary outcome measures will also include participant-centered assessment at T1.	Primary outcome: Assessment of resting-state functional connectivity at baseline (T0) and at the end of HomeCoRe (T1 after 6 weeks). Secondary outcome: Global cognitive and neuropsychological changes at T1, T2, and T3 vs. T0 when applicable according to Table 1. Secondary outcome measures will also include participant-centered assessment at T1.	Primary outcome: Assessment of resting-state functional connectivity at baseline (T0) and at the end of SMRT (T1 after 6 weeks). Secondary outcome: Global cognitive and neuropsychological changes at T1, T2, and T3 vs. T0 when applicable according to Table 1. Secondary outcome measures will also include participant-centered assessment at T1.	Primary outcome: Assessment of resting-state functional connectivity at baseline (T0) and at the end of sham intervention (T1 after 4 or 6 weeks). Secondary outcome: Global cognitive and neuropsychological changes at T1, T2, and T3 vs. T0 when applicable according to Table 1. Secondary outcome measures will also include participant-centered assessment at T1.

The primary active condition involves administering the NBCT protocol to 40 subjects with MCI across all included centers. The HomeCoRe protocol, involving 5 subjects, will be conducted exclusively in Pavia, while the SMRT protocol, involving 10 subjects, will be implemented only in Rome. The control condition consists in an unstructured home-based cognitive stimulation, involving 60 min of daily activities, with MCI sample size, frequency and overall treatment duration adapted to the experimental treatment of comparison. For each session, newspaper articles will be provided for the patient to read and summarize in a diary by answering specific questions. The protocol is administered remotely through TR with online assistance from a therapist.

Each patient will undergo brain rs-fMRI or HD-EEG acquisitions before (T0) and after (T1) active or control interventions.

Follow-up in-person neuropsychological assessments will be scheduled within 2 weeks from the end of the rehabilitation program (T1), and after 6 (T2) and 12 months (T3).

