### Control for confounding variables and biases

After baseline assessment, patients included in the study will be randomly allocated to two groups in a ratio of 1:1 based on active and control interventions, controlling for sex and education levels. We will generate random numbers with a computer algorithm^1^ from a uniform distribution in the range 0–1, dividing the range into two equal intervals and assigning each participant to the group corresponding to the sampled number (1,1 ratio). Stratification will be employed to ensure equal distribution of participants within each stratum (e.g., blocks based on sex and education level), and block randomization will be used within each block. Propensity score matching will be applied using logistic regression and matching participants based on similar scores, to ensure comparable groups.

Neuropsychologists carrying out cognitive evaluations will be blinded to group allocation to prevent bias. They will receive appropriate instruction and guidance regarding all assessment procedures and outcome parameters. Reminders (e.g., written reminders, phone calls, and email messages) for each visit will be sent to all participants to ensure compliance and complete data collection.

Not all outcome measures will be administered at each time point (summary in Table 2).

**Table 2 tab2:** Evaluation battery across testing sessions.

	T0	T1	T2	T3

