### Outcome measures

#### Primary outcome measures

Our primary goal is to understand how TR may affect RSNs communications in participants diagnosed with MCI due to a neurodegenerative disease. Primary outcomes will be measured through the assessment of changes in resting-state brain connectivity obtained from HD-EEG and rs-fMRI techniques. This would enable monitoring variations in resting-state connectivity involved during rehabilitative activities. Resting-state brain connectivity plays a critical role in deactivation during specific tasks, but this process becomes compromised with aging and progression toward neurodegenerative diseases. Consequently, interventions aimed at restoring brain connectivity have the potential to provide cognitive benefits in the early stages of the disease.

We plan to assess rs-fMRI FC and/or HD-EEG SA at two time points: before the TR (T0) and within 2 weeks of TR completion (T1). All the obtained measures will be compared with the results obtained from the MCI participants assigned to the control groups.

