### Planned analysis

#### Primary outcome analysis plan

Brain connectivity measures will be extracted from both rs-fMRI and HD-EEG data. The RSNs will be constructed considering a predetermined set of seed regions (Franco et al., 2013). As we will, for the first time, investigate the efficacy of three distinct TR approaches and their associated neural correlates, we will examine brain connectivity across all major RSNs.

For rs-fMRI seed-based timecourses will be extracted from each seed region, and individual maps of functional connectivity will be computed modeling the linear association between the timecourse of the seed and the timecourse of each voxel within the identified RSNs. For HD-EEG data, brain connectivity will be extracted by assessing the weighted Phase Lag Index (wPLI) (Vinck et al., 2011) that measures the phase synchronization of two signals. For both methods, the strength of the relationship between nodes of RSNs will be quantified using seed-based analysis, estimating pairwise correlations between a seed region and all the other voxels across the brain.

We will assess if the TR intervention has effects on changes in functional connectivity between T0 and T1 and whether these effects are absent at T0 vs. T1 in the control stimulation. This approach enhances the validity of the analyses by specifically addressing the impact of the treatment on connectivity changes over time and comparing them with a control condition.

Using the formula (Δ connectivity change = T1 − T0), the changes in Pearson’s correlation coefficient transformed into z-scores will be computed for each participant within each network. A large Δ connectivity change will represent a higher correlation coefficient (stronger connectivity) at T1 than T0.

The effect of the cognitive training program on network connectivity will be tested using mixed-design full-factorial scripts modeling the condition-by-timepoint interaction (increases Δ connectivity change seen in the experimental condition net of the increases seen in the control condition). We will also test the “inverse interaction” contrast (exclusive increases in Δ connectivity change seen in the control condition) as a methodological control. The statistical model will be run independently for each considered TR approach (i.e., NBCT, HomeCoRe, and SMRT).

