To account for the nested data structures (e.g., patients nested within different centers), we will employ multilevel modeling (MLM). MLM will allow us to partition the variance at different levels (e.g., within-patient, between-patient, and between-center) and accurately estimate the effects of the cognitive training program while accounting for potential clustering. This approach will help in managing the hierarchical nature of the data, improving the precision of our estimates.

Potential confounding variables (center of acquisition, MCI subtype, age, sex, functional activities, current pharmacological treatment, cognitive reserve) will be considered as covariates.

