#### Secondary objective analysis plan

Differences in global cognitive and neuropsychological performance scores, as well as caregiver burden assessments will be independently assessed using a two-way repeated measures ANOVA model, including assessment times and the TR interventions (active vs. control) as factors. The interaction between time and type of TR intervention will be investigated. To explore the variability in the trajectories of global cognitive and neuropsychological performance scores, individual items will be independently assessed using repeated measures linear mixed models. The time elapsed between assessments will be used to estimate the monthly rate of change, considering the type of TR intervention (active vs. control) as a main effect.

Furthermore, a linear correlation analysis will be applied to test the relationship between changes in connectivity from T0 to T1 and cognitive change over time. As mentioned above, the analyses will be conducted separately for each type of treatment/outcome and individual performance parameter.

We will re-run all the aforementioned analyses, stratifying by MCI subtype (aMCI and PD-MCI), to evaluate the disease-specific effects of TR on brain connectivity.

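### The plan does not say whether rs-fMRI and HD-EEG changes are pooled or analysed separately, and the stated sample size supports neither raw pooling nor separate tests

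*Protocol article*

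**What the plan says.** **Who is measured how.** The Study design section, after Table 1, states: "Each patient will undergo brain rs-fMRI or HD-EEG acquisitions before (T0) and after (T1) active or control interventions". Primary outcome measures is looser: "We plan to assess rs-fMRI FC and/or HD-EEG SA at two time points". The first gives one modality per patient and the second allows both. No section gives the share of patients per modality, or says how or when a patient's modality is chosen.

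**How the change is analysed.** The Primary outcome analysis plan describes a different extraction for each modality, then a single change score (T1 minus T0, as z-transformed Pearson correlations) and a single condition-by-timepoint model. The only split it states is by programme: "The statistical model will be run independently for each considered TR approach (i.e., NBCT, HomeCoRe, and SMRT").

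**Covariates and allocation.** The covariate sentence reads: "Potential confounding variables (center of acquisition, MCI subtype, age, sex, functional activities, current pharmacological treatment, cognitive reserve) will be considered as covariates". Centre is there and modality is not. Under Control for confounding variables and biases, allocation is "in a ratio of 1:1 based on active and control interventions, controlling for sex and education levels". Strata are given by example ("e.g., blocks based on sex and education level), and block randomization will be used within each block"), and modality is not one of them.

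**Sample size.** The Power analysis section takes d = 0.5, a significance level of 0.05 and power of 0.90, and arrives at about 80 NBCT participants, 40 per condition, without mentioning modality.

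**The concern.** A haemodynamic correlation and an electrical synchrony measure need not share a unit, a variance or an average change over time. The text does not make them comparable. For EEG the analysis plan says "For HD-EEG data, brain connectivity will be extracted by assessing the weighted Phase Lag Index (wPLI"), while the HD-EEG section specifies a Pearson correlation, and the change formula is written for Pearson only. The type of z-score is not defined.

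Centre cannot be relied on to carry modality. The MRI section puts a 3 T scanner in every centre, and the HD-EEG section has EEG recorded across centres.

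Two analyses are therefore open for the primary outcome. One puts raw scores from both modalities into one model, so the arm effect becomes a mixture weighted by measurement scale. The other runs a model per modality, so each test has fewer patients than the sample size assumes and no rule turns two results into one conclusion per programme. The choice could be made after the data are seen.

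**Working it through.** **Inputs**
- From the Power analysis section: 40 per arm, d = 0.5, significance level 0.05, target power 0.90. Sidedness is not stated; two-sided is assumed.
- Assumed, because the protocol gives no figure: an effect of 0.5 SD within each modality on its own scale; share p on the modality with the smaller SD (50:50, then 75% and 25%); ratio R of the larger to the smaller change SD (2, 3, 5).

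**Step 1: the plan's own figure.** Per arm, n = 2(1.960 + 1.282)² / 0.5² = 84.1, so 85 per arm (170 in total). At 40 per arm the noncentrality is 0.5 × √(40/2) = 2.236 and t-test power is 0.598. The stated inputs alone do not give 80. That is a separate problem, and 0.598 serves here only as the baseline. So that this point does not depend on it, results are repeated for d = 0.734, the effect that has 90% power at 40 per arm.

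**Step 2: raw scores pooled.** With SDs 1 and R and a difference Δ in mean change between modalities, the effective standardised effect is

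d_eff = d × [p + (1 − p)R] / √[p + (1 − p)R² + p(1 − p)Δ²].

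At p = 0.5 and Δ = 0:

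| R | d_eff for d = 0.5 | Power, d = 0.5 | Power, d = 0.734 |
|---|---|---|---|
| 1 | 0.500 | 0.598 | 0.900 |
| 2 | 0.75/√2.5 = 0.474 | 0.554 | 0.868 |
| 3 | 1.0/√5 = 0.447 | 0.506 | 0.826 |
| 5 | 1.5/√13 = 0.416 | 0.451 | 0.770 |

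At d = 0.5 and R = 2, 3, 5, power is 0.551, 0.481 and 0.386 with 75% on the smaller-SD modality, and 0.573, 0.551 and 0.527 with 25%. Equal SDs with Δ = 1 SD give d_eff = 0.5/√1.25 = 0.447 and power 0.506.

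**Step 3: separate models.** At 20 per arm the noncentrality is 0.5 × √(20/2) = 1.581 and power is 0.338 (0.619 at d = 0.734). With a 30/10 split per arm, power is 0.478 and 0.185 (0.798 and 0.343 at d = 0.734).

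**Step 4: estimated within modality, then combined.** In SD units each within-modality difference has variance 2/20 = 0.10, and the average of the two has variance 0.05. Then 0.5/√0.05 = 2.236, the same as in Step 1. Power stays at 0.598 (0.900 at d = 0.734).

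**Step 5: chance imbalance.** If 40 of the 80 have EEG, the number in one arm has SD 2.25 without stratification. The probability that the arms differ by 8 or more (for example 24 against 16) is about 0.12. This is how often imbalance occurs, not the size of an error in the effect. It matters only if mean change differs between modalities.

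**The case against.** A reader might infer that the protocol pools the two modalities on one error term. The documents do not say so, and several places fit separate analyses better. The Secondary objective analysis plan says: "As mentioned above, the analyses will be conducted separately for each type of treatment/outcome and individual performance parameter". It sits in the secondary plan but refers back, and outcome type could include modality. The MRI section adds intracranial volume as a covariate, which belongs to the MRI analysis and also shows that the main covariate list is not complete. EEG connectivity is examined in every frequency band, and no step reduces the bands to one score that could stand beside an fMRI score. Strata are given as examples, so that list may not be complete either. Pooling is therefore one reading and not a stated fact.

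The pooling loss is modest at moderate ratios: about 4 points of power at R = 2 and 9 at R = 3. If the z-scores were standardised within modality, most of the scale problem would go. If every patient had both modalities, separate tests would each keep 40 per arm, but the Study design sentence says one or the other.

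A reader might also infer that unbalanced modality biases the comparison. If modality is fixed before a 1:1 allocation, imbalance adds error but no expected bias. The protocol does not say when modality is fixed.

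The article is condensed, and modelling detail may sit in a fuller document. That covers part of the point only. The article itself sets the model split, the covariates, the allocation factors and the sample size. A later analysis plan cannot stratify patients who are already randomised. The separate reading also leaves the sample-size statement unsupported.

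**Conclusion.** The concern holds as a gap with consequences under both open readings, not as proof that unlike measures are pooled. With a 50:50 split and d = 0.5 within modality, raw pooling lowers power at 40 per arm from about 0.60 to between 0.55 and 0.45 for SD ratios of 2 to 5. Separate testing leaves about 0.34 at 20 per arm. Had the trial 90% power at 40 per arm, the corresponding figures would be 0.87 to 0.77 and 0.62. The sizes depend on a modality split and SD ratios that the protocol does not give. Two conclusions do not depend on those values: the analysis of the primary outcome by modality is not fixed, and a calculation for 40 per arm does not describe a test on part of those patients.

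**What to change.** **Primary outcome analysis plan.** State that the arm effect is estimated within modality and that raw scores are never pooled. If one result per programme is wanted, standardise the change within modality and fit modality, modality-specific residual variance and arm. Combining the two within-modality estimates with prespecified weights is an alternative. A modality term alone would remove a mean shift but not unequal variances. Report the modality-specific effects beside any combined figure, because the two may not measure the same quantity. State the EEG metric once and define the z-score.

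**Power analysis.** If the analyses stay separate, restate power for the number expected per modality.

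**Allocation.** For patients not yet randomised, fix modality before allocation and add it as a stratification factor, at least for NBCT. HomeCoRe and SMRT have 5 and 10 per arm, where another stratum may not be workable.

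**Consistency.** Reconcile Study design with Primary outcome measures on one or both modalities. State which measure enters any combined estimate when a patient has both.

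**Cost.** Analysis wording, a revised power statement, one more stratum level for the remaining patients and slightly more analysis work.

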#### Secondary objective analysis plan

Differences in global cognitive and neuropsychological performance scores, as well as caregiver burden assessments will be independently assessed using a two-way repeated measures ANOVA model, including assessment times and the TR interventions (active vs. control) as factors. The interaction between time and type of TR intervention will be investigated. To explore the variability in the trajectories of global cognitive and neuropsychological performance scores, individual items will be independently assessed using repeated measures linear mixed models. The time elapsed between assessments will be used to estimate the monthly rate of change, considering the type of TR intervention (active vs. control) as a main effect.

Furthermore, a linear correlation analysis will be applied to test the relationship between changes in connectivity from T0 to T1 and cognitive change over time. As mentioned above, the analyses will be conducted separately for each type of treatment/outcome and individual performance parameter.

We will re-run all the aforementioned analyses, stratifying by MCI subtype (aMCI and PD-MCI), to evaluate the disease-specific effects of TR on brain connectivity.

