**Discussion:**

The results of this RCT will identify a potential association between improvement in performance induced by individual cognitive TR approaches and modulation of resting-state brain connectivity. The knowledge gained with this study might foster the development of novel TR approaches underpinned by established neural mechanisms to be validated and implemented in clinical practice.

**Clinical trial registration:** [https://classic.clinicaltrials.gov/ct2/show/NCT06278818], identifier [NCT06278818].

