#### Secondary outcome measures

As the secondary outcome measures, we will consider the longitudinal changes in all the neuropsychological tests, questionnaires, and scales (T1, T2, and T3 vs. T0 when applicable according to Table 1). Secondary outcome measures will also include participant-centered outcomes to assess those aspects that are most important for the participants and the subjective evaluation of intervention success at T1. We will also correlate these findings with changes in FC/SA between T0 and T1. Furthermore, we will evaluate caregiver burden at different time points.

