### Power analysis

In line with the findings from De Marco et al. (2017), where increased DMN resting-state connectivity was observed in patients assigned to the experimental condition in a midline cluster extending to the precuneus and cuneus, we aim to detect similar changes in brain functional connectivity through our study. De Marco et al. reported decreased connectivity in the right and left parietal cortices for the control condition. The experimental condition showed an average increase of 0.18 z scores, while the control condition exhibited an average decrease of 0.63 z scores (mixed-design ANOVA’s F1, 35 = 15.08, *p* < 0.001). Based on these findings, we conducted a power analysis to determine the necessary sample size for detecting differences in functional connectivity changes between the experimental and control groups. Assuming a medium effect size (Cohen’s *d* = 0.5), a significance level of 0.05, and a power of 0.90, our analysis indicated that a total sample size of approximately 80 participants (40 per condition, evaluated at two time points for NBCT) would be sufficient to detect medium to large effects, ensuring robust and reliable results.

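### Connectivity–cognition correlations are planned for every programme, network and test score with no key pair, so programme-level associations should be explored, not identified

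*Protocol article*

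**What the plan says.** In the Protocol article, the Secondary objective analysis plan states that "a linear correlation analysis will be applied to test the relationship between changes in connectivity from T0 to T1 and cognitive change over time", and that "the analyses will be conducted separately for each type of treatment/outcome and individual performance parameter". It then repeats all analyses within the aMCI and PD-MCI subtypes.

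The size of the set follows from other sections:

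- **Networks.** The Primary outcome analysis plan computes one connectivity change per participant per network and says "we will examine brain connectivity across all major RSNs". It does not say how many there are.
- **Programmes.** The models are run separately for NBCT, HomeCoRe and SMRT.
- **Scores.** For secondary outcomes, "we will consider the longitudinal changes in all the neuropsychological tests, questionnaires, and scales" at T1, T2 and T3 against T0 where applicable. These findings are also to be correlated with the connectivity change.

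The Discussion paragraph of the abstract opens with this association: the results "will identify a potential association between improvement in performance induced by individual cognitive TR approaches and modulation of resting-state brain connectivity". The only significance level in the article is in the Power analysis ("a significance level of 0.05, and a power of 0.90"), where it serves the sample size of the primary NBCT comparison.

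**The concern.** The plan fixes a large set of separate correlations, each described as testing a relationship, and singles out none of them. The abstract then gives first place to an association for individual programmes. With this many chances, some pairs will probably look significant even if connectivity change and cognitive change are unrelated.

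The smallest programmes add a second problem. With so few participants, only a very large sample correlation can reach significance, so any pair that does will look like a strong brain–behaviour link. At stake is whether the trial can say that a given programme's cognitive gain goes with a change in connectivity. The primary outcome is not affected.

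**Working it through.** The article states no error rate or number of tests for the correlations, so it has no figure of its own to reproduce. Its sample-size figure concerns a different comparison.

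**Inputs from the article**

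- Programmes: 3, with 40, 5 and 10 active participants and the same numbers of controls (Table 1). Pooling arms gives n = 80, 10 and 20 for NBCT, HomeCoRe and SMRT.
- Cognitive scores (Table 2): 14 test rows, or 19 scores when immediate/delayed recall, forward/backward span and TMT A/B are counted separately.
- Follow-up changes: up to 3 per score.

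**Assumptions**

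- Each correlation is judged at two-sided 0.05. Neither the level nor the sidedness is stated for these analyses.
- Number of networks: 1 to 7.
- Equal pairwise correlation of 0.3 to 0.7 among scores and among networks.
- Arms pooled or active only; both were run because the article does not say which.

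**Step 1: independent tests.** The chance of at least one false positive in m tests is 1 − 0.95^m, and the expected number is 0.05 × m.

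- 3 × 14 = 42 tests: 1 − 0.95^42 = 88.4%; 2.1 expected.
- 3 × 19 = 57 tests: 1 − 0.95^57 = 94.6%; 2.9 expected.
- 57 × 7 networks = 399 tests: over 99.99%; 20 expected.

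**Step 2: correlated tests.** Simulation with no true link (1,000 runs per setting), T1 change only. The ranges span 14 or 19 scores, pooled or active-only samples, and correlations of 0.3 to 0.7.

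| Networks | Tests | Chance of at least one false association |
|---|---|---|
| 1 | 42 or 57 | 60% to 92% |
| 2 | 84 or 114 | 78% to 99% |
| 4 | 168 or 228 | 92% to 100% |
| 7 | 294 or 399 | 97% to 100% |

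The low end of each range comes from 14 scores correlated at 0.7. With 57 tests and one network the range is 66% to 92%. Dependence lowers the chance of any false positive but not the expected number: about 20 for 399 tests.

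NBCT alone (n = 80, 19 scores, one network) gives 30% to 53%. Seven networks with three follow-up changes (3 × 19 × 7 × 3 = 1,197 tests) gave at least one false association in every run.

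EEG frequency bands, questionnaires and the subtype re-runs are left out; they would add tests.

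**Step 3: smallest correlation that is significant.** Critical |r| = t / √(n − 2 + t²), where t is the 97.5% point on n − 2 degrees of freedom.

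- n = 5 (HomeCoRe active): t = 3.182; 3.182 / √(3 + 10.13) = 0.88.
- n = 10 (HomeCoRe pooled, or SMRT active): t = 2.306; 2.306 / √(8 + 5.32) = 0.63.
- n = 20 (SMRT pooled): 0.44.
- n = 80 (NBCT pooled): 0.22.

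**Step 4: is one named test feasible?** Power for a true r = 0.3 by Fisher's z is Φ(atanh(0.3) × √(n − 3) − 1.96). For n = 80 this is Φ(0.3095 × 8.775 − 1.96) = Φ(0.756), about 78%. The same formula gives 25% at n = 20 and 13% at n = 10.

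**The case against.** A reader might infer that the plan declares an association wherever p < 0.05, and that a false one is therefore near certain. The article supports neither statement. It gives no level and no reporting rule for the correlations; 0.05 is carried over from the power paragraph. The number of networks is not stated, and with one network and T1 change only the chance can be as low as about 60%. Cognitive change over time may also mean one slope per score, in which case the threefold count over visits does not apply.

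A reader might also infer that no multiplicity control is planned. These are secondary analyses in a condensed article, and an adjustment may sit in an analysis plan that is not shown. Its absence here is not the finding.

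Nor does the abstract promise an established link. It calls the association potential, says only that the knowledge might help new approaches, and expects those to be validated. It would also go too far to say that the plan cannot tell a real link from none: effect sizes and consistency across related scores in NBCT would still carry information.

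These points remove the unconditional claim. What remains is what the article itself fixes: separate correlations over every programme, network and score, with no key pair, feeding a conclusion about individual programmes. The word potential does not label the analysis exploratory. The later remark about confirmatory trials, in the limitations, concerns feasibility and efficacy rather than this association. An adjustment elsewhere would not change the abstract or make n = 5 or n = 10 informative.

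**Conclusion.** The concern holds in conditional form. If the correlations are judged one by one at two-sided 0.05, at least one false association is likely with a single network and very likely with four or more. One network is a floor, since the article speaks of all major networks in the plural. These figures rest on the assumed level, the assumed correlations among scores and networks, and a network count that is not given.

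The point about small programmes needs no network count. At 0.05, a HomeCoRe correlation is significant only when it is very large, so association claims for that programme are not supportable. SMRT is only somewhat better placed.

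**What to change.** 1. **Secondary objective analysis plan.** Label the whole set of connectivity–cognition correlations exploratory, state how many there are, and apply false-discovery-rate control over the NBCT set. For HomeCoRe and SMRT, report estimates with confidence intervals and make no significance claims.
2. **If a confirmatory association is wanted.** Pre-specify one connectivity measure against one cognitive composite in the NBCT comparison (n = 80). The choice of pair is the sponsor's; it should be weighed against the stated reason for examining all major networks, because a single pair may miss a link elsewhere.
3. **Abstract, Discussion.** Say that the trial will explore potential associations, in place of identifying one.

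The cost is protocol or SAP wording, plus a simple composite score if step 2 is taken. No new data are needed. The downside is that isolated test-level correlations could no longer be claimed as findings.

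### Separate re-runs in aMCI and PD-MCI cannot show that the training effect differs by subtype, and no analysis named in the article estimates that difference

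*Protocol article*

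**What the plan says.** The last sentence of the secondary objective analysis plan gives both a method and its purpose: "We will re-run all the aforementioned analyses, stratifying by MCI subtype (aMCI and PD-MCI), to evaluate the disease-specific effects of TR on brain connectivity".

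The models to be repeated are described just before it. The primary analysis works by "modeling the condition-by-timepoint interaction". The secondary analysis uses a repeated-measures ANOVA with a time-by-intervention interaction, plus linear mixed models with intervention as a main effect. In the primary plan, subtype has one role: "Potential confounding variables (center of acquisition, MCI subtype, age, sex, functional activities, current pharmacological treatment, cognitive reserve) will be considered as covariates".

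Two further statements set the scale of the re-runs. On the three approaches: "The statistical model will be run independently for each considered TR approach". On the networks: "we will examine brain connectivity across all major RSNs". Table 1 gives 40 per arm for NBCT, 5 for HomeCoRe and 10 for SMRT. The eligibility criteria admit both subtypes with no stated quota, and subtype is not among the examples given of stratification factors.

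**The concern.** Whether training acts differently in the two diseases is a question about a difference between two effects. Two separate analyses, each testing its effect against zero, do not estimate that difference. A significant result in one subtype and a non-significant one in the other can arise easily when the true effects are equal, because each subgroup is small and the larger one has more power.

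The covariate role does not fill the gap. A main-effect term for subtype allows the two diseases to differ in level or average change, but it holds the training effect common to both. The named interactions (condition by timepoint, time by intervention) do not involve subtype.

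At stake is a possible report that training alters connectivity in one disease and not the other, with no estimate behind the contrast. The comparison would be available for every network and every neuropsychological score, which gives many chances for such a pattern to appear.

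**Working it through.** **Inputs.** From the article: NBCT 40 per arm (Table 1; Power analysis), planning effect d = 0.5 and alpha 0.05 (Power analysis), 5 and 10 per arm for HomeCoRe and SMRT (Table 1). Assumed: two-sided tests, one test per network, equal SDs, and subtype splits from 20/20 to 32/8 per arm, since the article gives none.

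**The plan's own figure.** There is no stated figure for the subtype analysis. The overall sample size, about 80 at d = 0.5 and 90% power, does not reproduce as a two-sample comparison of change: 40 per arm gives power 0.60. About 80 is reached only with a correlation that the article does not state. That is a separate matter, and this point does not depend on it.

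**Step 1: power within a subtype.** With n per arm, use the noncentral t with 2n - 2 degrees of freedom and noncentrality d x sqrt(n/2). At d = 0.5 power is 0.338 for n = 20, 0.478 for n = 30, 0.185 for n = 10, 0.504 for n = 32 and 0.154 for n = 8.

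**Step 2: chance that exactly one subtype is significant.** With powers p1 and p2 in independent subgroups, this is p1(1 - p2) + p2(1 - p1).

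- 20/20: 2 x 0.338 x 0.662 = 0.447
- 30/10: 0.478 x 0.815 + 0.185 x 0.522 = 0.486
- 32/8: 0.504 x 0.846 + 0.154 x 0.496 = 0.503

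The same formula, with the same true effect in both subtypes throughout, gives:

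| True d in both | 20/20 | 30/10 | 32/8 |
|---|---|---|---|
| 0 | 9.5% | 9.5% | 9.5% |
| 0.2 | 17% | 17% | 17% |
| 0.5 | 45% | 49% | 50% |
| 0.8 | 43% | 58% | 64% |
| 1.0 | 23% | 44% | 54% |
| 1.28 | 5% | 23% | 34% |

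The last row converts the F(1,35) = 15.08 quoted in the Power analysis: d = 2 x sqrt(15.08)/sqrt(37) = 1.28, assuming about 37 people in two equal groups. A direct interaction test would wrongly declare a difference 5% of the time in every cell.

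**Step 3: what the interaction can deliver.** In SD units of change, its standard error is sqrt(2/a + 2/b), with a and b per arm in the two subtypes. This is 0.447 at 20/20 and 0.516 at 30/10, or 2.0 and 2.3 times the overall NBCT standard error of sqrt(2/40) = 0.224. Power for a true difference of 0.5 SD is about 0.20 and 0.16. The 95% interval is about plus or minus 0.88 SD (1.96 x 0.447) to 1.01 SD (1.96 x 0.516).

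**Step 4: the two small comparisons, at d = 0.5.** HomeCoRe split 2 and 3 per arm has 6-8% power in each subtype, and exactly one is significant 13% of the time. SMRT has 6-15% power and a rate of 19-20%.

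**The case against.** A reader might infer that the plan contains a rule under which significance in one subtype only will be declared disease specificity. It does not. The sentence says that analyses will be repeated by subtype and for what purpose; it does not say how the two sets of results will be compared. It can be read as describing the effect within each disease, for which stratified estimates are a legitimate display. The harm therefore depends on how the re-runs are read.

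A reader might also infer that a misleading one-subtype pattern is likely whatever the truth. The documents do not support that either. The rate depends on a true effect and a subtype split that the article does not give. A stricter threshold, plausible for voxel-level maps, also changes it: at an illustrative alpha of 0.005 and d = 0.5 it is 17-21%, while at d = 0.8 it is 45-60%.

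The full statistical analysis plan is not shown and may contain an interaction term. The claim is confined to what the article names. This is still more than missing detail, because the article states a method for a stated purpose and the method cannot settle whether the effects differ.

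Finally, the interaction is underpowered. That is true, but the separate re-runs hold no more information about the difference; they only leave its uncertainty unreported.

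**Conclusion.** The point holds in a limited form. The article names separate re-runs as the means of judging effects specific to each disease, and no analysis it names estimates whether the training effect differs by subtype.

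If the NBCT re-runs were compared by significance, a one-subtype-only result would arise about 45-50% of the time at the protocol's own planning effect with no true difference, against 5% for an interaction test. That figure rests on the assumptions listed with the calculation, and the range over other effects runs from about 5% to 64%.

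In HomeCoRe and SMRT the difficulty is different. The likeliest result is no significance in either subtype, so the splits are uninformative rather than misleading. The full-sample primary analysis is not affected. The matter concerns a secondary analysis in a study that its Discussion presents as groundwork for larger confirmatory trials.

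**What to change.** In the NBCT comparison, add a condition-by-subtype term to the change model, and condition-by-time-by-subtype to the repeated-measures models. Report the aMCI effect, the PD-MCI effect and the interaction from that model with 95% confidence intervals, labelled exploratory. State that any claim that effects differ by disease rests on the interaction estimate alone, and that a non-significant interaction will not be read as equal effects. For HomeCoRe and SMRT, present any subtype results descriptively, without subtype testing.

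The cost is a change of wording and one added term per model. Recruitment, assessments and interventions are unchanged. The downside is that the likely result is a wide interval that leaves the question open.
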